## 2 AIMS AND OBJECTIVES

### 2.1 Main Trial Objectives

#### 2.1.1 Clinical Aims and Objectives

To evaluate whether in children undergoing cardiac surgery with cardioplegic arrest, the use of del Nido cardioplegia, compared with St. Thomas' blood cardioplegia:

- reduces myocardial injury, as determined by AUC for plasma troponin following surgery
- reduces the duration of ischaemia (aortic cross-clamp time), the volume of cardioplegia given, and the need for internal defibrillation during reperfusion
- improves myocardial protection, reducing the frequency or severity of LCOS, and markers of reduced tissue perfusion (arterial lactate and *omega*)
- improves other clinical outcomes, including duration of mechanical ventilation, length of stay on the Paediatric Intensive Care Unit and in hospital, and 30-day survival

#### 2.1.2 Mechanistic Aims and Objectives

To determine whether in children undergoing cardiac surgery with cardioplegic arrest, the use of del Nido cardioplegia, compared with St. Thomas' blood cardioplegia, impacts on changes in the metabolic profile of the myocardium during ischaemia.

## 3 TRIAL DESIGN AND SETTING

### 3.1 Trial Design

The DESTINY trial is a phase II/III, 2 arm, multi-centre, participant-blinded, assessor-blinded, parallel-group, individually randomised controlled trial with allocations on a 1:1 basis.

#### 3.1.1 Trial Setting

The trial will take place at a number of Level 1 paediatric cardiac surgery centres in the UK, with the potential to expand to more centres in the event of local issues delaying set-up or restricting recruitment once open.

#### 3.1.2 Identification of participants

At the participating centres potential participants fulfilling the inclusion/exclusion criteria will be identified from the multi-disciplinary team meeting, surgical waiting list, clinic, or ward by the patient's direct clinical care team, i.e. Consultant or Specialist Nurse. Electronic and/or paper healthcare records will be used to identify suitable patients and determine eligibility.

Following identification by the clinical team, the potential participant will then be referred to the DESTINY research team. The parent/guardian(s) +/- child will be approached by a delegated member of the clinical or research team. The Patient Information Sheet (PIS) will be provided either in person or by post and the parent/guardian(s) will be given sufficient time to read the PIS, consider participation and ask questions (see section 5).

In those willing to participate in the trial, written informed consent will be obtained by a member of the research team who will have up to date GCP training, in depth knowledge of the study protocol and have been delegated authority from the local Principal Investigator. Their name will be recorded on the [DESTINY Site Signature and Delegation Log](#). Upon obtaining of informed consent, baseline data will be collected.

The outcome of the conversation, i.e. whether the parent/guardian(s) agreed to participation, have given informed consent, and have been randomised to the trial will be recorded in the trial screening log. This will be necessary for assessing recruitment feasibility and for future conversations with the patient should they wish to have more time to consider participation to the trial.

#### 3.1.3 Sub-studies

The trial intends to incorporate several potential sub-studies:

- **Qualitative sub-study:** Semi-structured interviews with surgeons and perfusionists to explore their experiences of using del Nido cardioplegia during the trial, to inform its potential implementation into routine NHS practice at the end of the trial.
- **Metabolic sub-study:** In a subset of patients, right atrial biopsies will be obtained soon after aortic cross-clamping (onset ischaemia) and just before its release (late ischaemia) to assess metabolic changes in the myocardium during ischaemia. The impact of cardioplegia type on metabolism will be assessed through pathway enrichment analysis, in collaboration with University of Liverpool.

- **Genetics sub-study:** With additional funding, genomic analysis will be performed to assess potential associations with markers of myocardial protection during surgery.
- **Imaging follow-up sub-study:** With additional funding, cardiac magnetic resonance (CMR) imaging and echocardiography will be used to assess late ventricular systolic and diastolic function at 5 years of age in a sub-group of patients aged 0-2 years at the time of surgery. Using core laboratory methodology to ensure data quality and standardisation, this sub-study will include non-invasive haemodynamic assessment and CMR tissue characterisation.

#### 3.1.4 Assessment of Risk

All clinical trials can be considered to involve an element of risk and, in accordance with BCTU operating procedures, this trial has been risk assessed, to clarify any risks relating uniquely to this trial. This risk assessment, on the basis that the IMP is not licensed within the EU, but there is extensive clinical evidence on its use in this patient group in both the USA and Spain, concluded that this trial is:

- Type B = Somewhat higher than that of standard medical care.

## 4 ELIGIBILITY

### 4.1 Inclusion Criteria

Children (<16 years) undergoing cardiac surgery on cardiopulmonary bypass with cardioplegic arrest.

### 4.2 Exclusion Criteria

- Predicted cross-clamp time <30 minutes (e.g. atrial septal defect, atrial septectomy, sub-aortic stenosis) at the discretion of the Consultant surgeon
- Known contraindication to one of the constituents of either cardioplegia solution (e.g. lidocaine/procaine hypersensitivity/allergy) or its method of delivery, including temperature (e.g. haemoglobinopathy including sickle cell disease, cold agglutinins)
- Weight at the time of screening >50kg
- Ventricular assist device (VAD) insertion/explant or transplantation
- Preoperative inotropic support or extra-corporeal life support (ECLS)
- Previous cardiac surgery with cardioplegic arrest within the last 30 days
- Previous enrolment in the DESTINY trial
- Emergency surgery
- Parent/guardian declines consent

### 4.3 Co-enrolment

Co-enrolment into cluster randomised trials is permitted, but not into any individually randomised controlled trial unless specifically agreed with the Trial Management group (TMG) in advance.

## 5 CONSENT

It will be the responsibility of the Principal Investigator or their delegate to obtain written informed consent for each participant prior to performing any trial related procedure. Research Nurses may be permitted to obtain informed consent if local practice allows, and this responsibility has been delegated by the Principal Investigator (PI) as captured on the Site Signature and Delegation Log.

A Parent/Guardian Participant Information Sheet (PIS) will be provided to facilitate this process. There are two versions of the PIS: *version a* is for use at sites with liquid nitrogen available to snap-freeze tissue biopsies and includes information on taking biopsies; *version b* is for use at sites without liquid nitrogen availability and does not include information on taking biopsies as this will not be performed at such sites. In addition, a Child/Young Person PIS will be provided to children aged 8 years and above, when appropriate. The Principal Investigator or their delegate will ensure that they adequately explain the aim, trial intervention, anticipated benefits, and potential hazards of taking part in the trial to the parent/guardian +/- participant. They will also stress that participation is voluntary and that they are free to decline to take part or may withdraw from any aspect of the trial at any time.

The parent/guardian +/- participant will be given adequate time (at least 12 hours) to read the PIS and to discuss their participation with others outside of the site research team. The parent/guardian +/- participant will be given the opportunity to ask questions and if they agree to participation in the trial, they will be asked to sign and date the latest version of the Informed Consent Form (ICF). Similarly, there are two versions of the ICF: *version a* is for use at sites with liquid nitrogen available and *version b* for use at sites without liquid nitrogen availability. The parent/guardian must give explicit consent for the regulatory authorities, members of the research team and or representatives of the sponsor to be given direct access to the participant's medical records. In addition, a Child/Young Person Assent form will also be used for those aged 8 years and above, when appropriate.

The ICF contains optional items relating to consent for: the use of blood samples taken during the trial in future research; the taking, storage, analysis and use in future research of tissue biopsies (*version a* only); the taking, storage and genetic analysis of blood samples; the use of data held by central NHS bodies (see below); and the retention of contact information to enable future contact for consideration of participation in follow-up studies. The parent/guardian may provide or decline consent for any of these items independently.

The Principal Investigator or delegate will then sign and date the ICF +/- Assent form; a copy will be given to the parent/guardian, a copy will be filed in the medical notes, and the original placed in the Investigator Site File (ISF). Once the participant is entered into the trial, their trial number will be entered on the ICF maintained in the ISF. In addition, if the parent/guardian has given explicit consent, a copy of the signed ICF will be sent to the Birmingham Clinical Trials Unit (BCTU) trial team for review.

Details of the informed consent discussions should be recorded in the participant's medical notes in accordance with Good Clinical Practice (GCP). This should include date of discussion, the name of the trial, outcome of the discussion, version number of the PIS given to the family, version number of ICF signed and date consent received, and that the person signing the

consent form on behalf of the child has been determined to have parental responsibility. If a translator has been used this should be noted in the patient medical records. A copy of PIS should also be added to the medical notes.

Throughout the trial, the parent/guardian +/- participant will have the opportunity to ask questions about the trial. Any new information that may be relevant to their continued participation will be provided. Where new information becomes available which may affect their decision to continue, they will be given time to consider and if happy to continue will be re-consented. Re-consent will be documented in the medical notes. The parent/guardian's right to withdraw the participant from the trial will remain.

Electronic copies of the site-specific PIS and ICF will be available from the DESTINY Trial Office to be printed at the local site. Details of all parents/guardians approached about the trial will be recorded on a **DESTINY Participant Screening and Enrolment Log** and with the parent/guardian's prior consent, their General Practitioner (GP) will also be informed that the participant is taking part in the trial.

This study includes an optional consent to allow linkage to patient data available in NHS routine clinical datasets, such as the Paediatric Intensive Care Audit Network (PICANet), Hospital Episode Statistics (HES) and mortality data from the Office of National Statistics (ONS) through The Health and Social Care Information Centre and other central UK NHS bodies. The consent will also allow access to other new central UK NHS databases that may appear in the future. It will allow us to cross-check relevant outcomes against routine data sources and extend the follow-up of patients in the trial and collect long-term outcome and health resource usage data without needing further contact with the study participants. This is important as it will link treatments that may become a clinical standard of care to long-term outcomes that are routinely collected in clinical data, but which will not be collected during the follow-up period of the trial.

## 6 ENROLMENT AND RANDOMISATION

### 6.1 Enrolment and Screening

Patient eligibility will be confirmed by a member of the research team who is medically qualified, i.e. by a doctor. All baseline assessments will be carried out after informed consent and prior to patient randomisation.

At baseline, prior to randomisation, the following assessments will be performed:

- Patient demographics
- Preoperative weight and height/length
- Resting oxygen saturations
- Preoperative haematocrit
- Comorbidities
- Preoperative medications

### 6.2 Randomisation

#### 6.2.1 Randomisation Methodology

Participants will be randomised by computer at the level of the individual in a 1:1 ratio to either del Nido cardioplegia or St. Thomas' blood cardioplegia.

A minimisation algorithm will be used within the online randomisation system to ensure balance in the treatment allocation over the following variables:

- Age: neonate (0-30 days), infant (31 days<1 year), child (1<7 years), older child (7<16 years)
- Incision or resection of ventricular myocardium anticipated (yes/no)
- Surgical centre

A 'random element' will be included in the minimisation algorithm, so that each participant has a probability (unspecified here), of being randomised to the opposite treatment that they would have otherwise received.

Full details of the randomisation specification will be stored in a confidential document at BCTU.

#### 6.2.2 Blinding

As the technique for delivery of cardioplegia and interval between doses necessarily differs between treatment groups, patient safety may be compromised by blinding those administering the cardioplegia. The operating surgeon, perfusionist, anaesthetist, theatre scrub team and research nurse therefore will *not* be blinded to the intervention.

However, as the cardioplegia is only administered during surgery, patients, parents/guardians, and outcome assessors such as cardiologists, other surgeons, PICU medical and nursing staff, and ward staff will be blinded to the allocation. This will be maintained by only documenting the use of cardioplegia in the medical notes without referring to which product was used.

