### 6.2.5 Randomisation Records

Following randomisation, a confirmatory e-mail will be sent to the randomiser (usually research nurse or perfusionist), DESTINY Trial Manager and CI.

Investigators will keep their own study file log which links participants with their allocated trial number in the **DESTINY Participant Recruitment and Identification Log**. The Investigator must maintain this document, which is **not** for submission to the Trials Office. The Investigator will also maintain the **DESTINY Participant Screening and Enrolment Log** which will be housed electronically on the REDCap database. The **DESTINY Participant Recruitment and Identification Log** and **DESTINY Participant Screening and Enrolment Log** should be held in strict confidence.

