| Control      | St Thomas' blood cardioplegia | 4:1 blood:crystalloid using Harefield Hospital preparation | Initial dose of 20-30ml/kg, subsequent doses of 15 ml/kg every 20-30 minutes, at the discretion of the surgeon |

**Table 2.** Acceptable formulations of IMP and dosage of experimental vs control arm.

The allocated cardioplegia solution will be administered according to the above preparation and schedule by the Clinical Perfusionist, at the request of the operating surgeon, in an antegrade manner via an aortic root or direct coronary ostia canula, following placement of a cross-clamp on the proximal aorta. The glass bottle containing the IMP should be vented using a spike vent or similar during infusion. By placing a waste sucker into the right atrium after commencing its delivery, the systemic bioavailability of the cardioplegia constituents following passage through the coronary circulation will be markedly reduced.

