## 9.4 Serious Adverse Event (SAE) Reporting in DESTINY

SAE reporting using standard definitions and practices for adult drug trials are not appropriate for clinical trials involving cardiac surgery in children [44] as events typically classified as SAEs occur commonly in the usual perioperative course for these children; their use would lead to a significant reporting burden and may detract from those events which are considered critical. A recent multi-centre UK study has defined important early morbidities associated with paediatric cardiac surgery as part of a wider study on morbidity in these patients [3], which have been adopted by the UK National Congenital Heart Disease Audit [45]. We therefore will use or adapt these definitions of important morbidities as the basis for expedited reporting of SAEs in this trial of children of all ages undergoing non-emergency cardiac surgery.

As the period of data collection lasts for 30 days, participants will remain under follow-up at the same hospital for the duration of their participation in the trial such that the local research team will collect all trial data on all events meeting the definition of SAEs directly. If the patient has been discharged home within 30 days, the occurrence of any SAE within this timeframe will be ascertained either during a routine follow-up clinic visit or by a telephone call.

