On receipt of an SAE Form, the Trials Office will forward it, with the unique reference number, to the Chief Investigator (CI) who will independently review the causality of the SAE. An SAE judged by the PI or CI to have a reasonable causal relationship with the intervention will be regarded as a related SAE (SAR). The causality assessment given by the PI will not be downgraded by the CI. If the CI disagrees with the PI's causality assessment, the opinion of both parties will be documented, and where the event requires further reporting, the opinion will be provided with the report. The CI will send their assessment of causality and, where applicable, expectedness (see 9.8 below) to the Trials Office.

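### Assessor blinding is not secured for ascertaining serious adverse events or judging their cause, because the research nurse is unblinded and the CI is sent the randomisation e-mail

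*Protocol*

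**What the plan says.** Section 3.1 of the Protocol describes the trial as "participant-blinded, assessor-blinded, parallel-group, individually randomised controlled trial", and the Trial Summary uses an equivalent label. Neither limits it to particular outcomes.

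Section 6.2.2 gives one reason for open allocation: "patient safety may be compromised by blinding those administering the cardioplegia". It then lists the open roles: "The operating surgeon, perfusionist, anaesthetist, theatre scrub team and research nurse therefore will" not be blinded. Patients, parents and outcome assessors are to be blinded. The assessors given as examples are cardiologists, other surgeons, and PICU and ward staff. Section 6.2.3 adds concealed perfusion charts, logged access to electronic charts and a PICU handover without cardioplegia details.

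Four other sections bear on the point:

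- Section 7.1: the solution is given "by the Clinical Perfusionist, at the request of the operating surgeon".
- Section 6.2.5: after randomisation, "a confirmatory e-mail will be sent to the randomiser (usually research nurse or perfusionist), DESTINY Trial Manager and CI".
- Section 9.4: "the local research team will collect all trial data on all events meeting the definition of SAEs directly". For children already at home, SAEs up to day 30 are found at a routine clinic visit or by telephone.
- Section 9.7.3: the PI gives the first causality opinion. The form then goes to the CI, "who will independently review the causality of the SAE". Under section 9.8 the CI also judges the expectedness of related SAEs.

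**The concern.** The reason in section 6.2.2 concerns people who deliver the product. It does not explain why a member of the team that gathers safety data should know the arm. Nothing in the protocol requires the person who makes the 30-day call, the person who completes the Postoperative CRF, the PI or the CI to be blind.

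Two things are at stake. The first is the safety comparison. If the person asking about or classifying an event knows the arm, softer events and events after discharge may be sought or coded differently between arms. If the CI knows the arm, events in one arm may more readily be called related. The second is the label. Readers of the results would take assessor-blinded to cover safety outcomes for which the protocol has not arranged it.

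**Working it through.** No arithmetic applies. The protocol gives no SAE rate and no measure of how complete ascertainment is. The check follows each role from knowledge of the allocation to the task done afterwards.

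| Role | Knowledge of allocation | Later task |
|---|---|---|
| Perfusionist | Open (6.2.2); delivers the product (7.1) | None stated in postoperative assessment |
| Research nurse | Open (6.2.2); often the randomiser (6.2.5) | Part of the local team that collects SAE data (9.4) |
| PI | Not stated | First opinion on causality and severity (9.7.3) |
| CI | Sent the randomisation e-mail (6.2.5); content not stated | Causality review (9.7.3) and expectedness (9.8) |
| PICU and ward staff, cardiologists, other surgeons | Blinded (6.2.2, 6.2.3) | Write the clinical record |
| Troponin laboratory | Not stated | Batched assay (8.3) |

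**Research nurse.** The stated reason reaches only those who administer the cardioplegia. Read literally, it does not reach the anaesthetist or scrub team either, but they are in theatre and cannot practically be blinded. For the nurse, the only other reason to be found is practical: the nurse is one of the two usual randomisers. The protocol does not present that as a justification, and the perfusionist is the other usual randomiser.

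**SAE data.** Table 7 in section 10.1 makes the original clinical record the source for clinical events. In hospital, that record is written largely by blinded staff, so a nurse who transcribes it has limited room to introduce bias. Two areas lie outside this protection. One is an event learned of by telephone, where the caller may be the first to record it. The other is an event that needs judgement to classify, such as sepsis in section 9.6 or the open-ended other categories in section 9.5.

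**CI.** Section 6.2.6 says expressly that the GP is not told the allocation. Section 6.2.5 has no such exclusion for the CI or Trial Manager. The same e-mail goes to the randomiser, who needs the allocation, so it is reasonable to assume that it shows it. Under section 9.7.3 the CI cannot downgrade the PI's opinion, but an event that either of them considers related becomes a serious adverse reaction. A CI opinion alone is therefore enough to move an event up. Related events go on to the same person for expectedness and SUSAR classification (9.8), and expedited SAEs go to the DMC (9.10.2).

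**When the allocation is needed.** Section 9.2 names different reference safety information for the two products, so expectedness cannot be judged without knowing the arm. Section 9.7.3 gives no step for which the CI must know it before recording causality.

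**The case against.** A reader might infer that the assessor-blinded label is untrue for the trial as a whole. The document does not support that. Bedside and ward assessors are blinded, charts and handover are controlled, clinical events are taken from the clinical record, and the primary outcome is a laboratory assay. Many secondary outcomes are times, infusion doses, creatinine values or survival. Death, ECLS, chest compressions, reoperation and imaging-confirmed stroke have explicit definitions and are hard to miss selectively.

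Other points on this side also have force:

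- The assessors in section 6.2.2 are examples, not a closed list.
- The nurse's open status is disclosed, not hidden.
- Section 9.4 names the local research team and does not say that the nurse makes the call. Tasks are assigned in a delegation log that is not shown.
- Causality is not a listed trial outcome.
- A nurse who attends theatre could not easily be blinded, because redosing intervals differ visibly between arms (60-90 against 20-30 minutes, section 1.1.9).

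These points narrow the concern to softer and post-discharge SAEs and to causality. They do not remove it. The blinding controls in sections 6.2.2 and 6.2.3 are set out in detail but do not reach the people who collect SAE data after discharge or review causality, and the label carries no limit.

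**Conclusion.** The point holds within limits. Assessor blinding is not secured for SAE ascertainment, chiefly post-discharge and softer events, or for SAE causality. The nurse limb rests on two stated facts: the role is unblinded for a reason that does not fit it, and it belongs to the team that collects SAE data. That a nurse makes the 30-day call is possible but not stated. The CI limb rests on the assumption that the randomisation e-mail shows the allocation. If it does not, that limb falls away unless the CI learns the arm by another route.

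The size of any bias cannot be derived from the document, and no figure is offered. The troponin comparison is little exposed, although the blinding of laboratory staff is not stated. This is a worthwhile, low-cost improvement to the safety comparison and the design label. It is no threat to the primary inference.

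**What to change.** 1. In section 6.2.5, send the CI and Trial Manager a confirmation that omits the allocation. In section 9.7.3, have the CI, and the PI where the PI is not the operating surgeon, record causality before seeing the allocation. Release it only when the expectedness of a related SAE has to be judged against the reference information for that product.
2. In sections 6.2.2 and 9.4, where existing staffing allows, have the perfusionist randomise and complete the Perfusion CRF under restricted access. A team member without access to the allocation should make the 30-day call and complete the Postoperative CRF. Section 10.4 already provides role-based security controls. Where the nurse stays open, give the actual reason.
3. In section 3.1 and the Trial Summary, limit the assessor-blinded label to the outcomes for which it is true. Cross-clamp time, cardioplegia volume and internal defibrillation arise in theatre under the open team and fall outside it in any case.

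Cost: wording changes in these sections, a revised e-mail template and a database permission. Some randomisation work moves to perfusionists. Where the nurse attends theatre, item 2 may not be achievable or may need another person; the label should then say so.
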